## Introduction

Gastro-oesophageal reflux disease (GORD) represents a significant burden on the Western healthcare system, affecting up to 20% of adults, with a rising prevalence^1,2^. GORD negatively impacts a patient’s health-related quality of life (HRQoL) and is associated with an increased risk of complications, including inflammation and strictures, Barrett’s oesophagus, and oesophageal adenocarcinoma^3^. Long-term use of proton pump inhibitors (PPIs) remains the mainstay of medical treatment for GORD; however, these may be associated with an increased risk of side effects, including dementia, renal pathology, infections, fractures, and gastric cancer^4^. A large UK RCT (REFLUX) showed that surgery (laparoscopic fundoplication) offers the most effective symptom control at 5-year follow-up, as well as being the most cost-effective treatment strategy when compared with medical therapy^5,6^.

Laparoscopic fundoplication is currently the ‘gold standard’ surgical treatment for managing GORD, with an excellent safety profile and a 30-day mortality risk of 0.03%^7^. The side effects are mainly gas bloating and inability to belch (up to 85%), dysphagia (3–24%), diarrhoea (18–33%), and recurrence of reflux symptoms (10–62%)^8,9^. Approximately 5% of patients undergoing fundoplication in England may require secondary surgery and 60% of patients use antireflux medication within 12 months of primary antireflux surgery^7^.

The introduction of the LINX device in 2007 provided a surgical alternative to fundoplication, requiring less extensive dissection and less disruption of the hiatal anatomy and natural antireflux mechanisms^10,11^. The LINX device is placed around the distal oesophagus and consists of titanium beads with a magnetic core that augments lower oesophageal tone and thus prevents reflux by mimicking normal anatomical antireflux mechanisms^12^. The LINX device, while augmenting the lower oesophageal sphincter, can accommodate the escape of elevated gastric pressure associated with belching or vomiting, which may reduce gas bloating. Complications of the LINX device include dysphagia, requiring dilatation at the site of the device in 5–11% of patients, and endoluminal erosions (0.1%) requiring device removal^11,13^.

In non-randomized comparative studies patients have reported favourable outcomes with LINX compared with fundoplication^13^. Aside from its ease of insertion, the LINX device is appealing in terms of symptom control, shorter operating time, reduced hospital stay, and lower burden of postoperative care^14^. A systematic review and meta-analysis of the laparoscopic LINX procedure *versus* laparoscopic fundoplication (consisting of 6 cohort studies and 1099 patients) showed no statistically significant differences between the groups in the requirement of postoperative antireflux medication, GORD-HRQoL scores, dysphagia, or reoperation. However, LINX was associated with significantly less gas bloating (pooled OR 0.34 (95% c.i. 0.16 to 0.71)) and a greater ability to belch (pooled OR 12.34 (95% c.i. 6.43 to 23.7))^13^. A further systematic review evaluated the introduction of LINX in the context of the established Idea, Development, Exploration, Assessment, and Long-term follow-up (IDEAL) framework^15^. Several IDEAL phase IIb studies were identified, with a lack of standardized surgical quality assurance (SQA) regarding LINX implantation and lack of consensus regarding results that should be evaluated to meaningfully assess patient benefit. This review concluded that studies that are well designed and well conducted are needed to evaluate the LINX procedure.

Although the National Institute for Health and Care Excellence (NICE) allows the use of the LINX device in clinical practice, it encourages research in this area, particularly trials that compare the LINX device with other forms of antireflux surgery^16^. The aim of this RCT is to test the hypothesis that the LINX procedure achieves similar reflux control and improves postoperative symptoms, specifically gas bloating and inability to belch, when compared with fundoplication at 24 months after surgery.

## Methods

### Design

The GOLF trial is an international, multicentre, pragmatic, two-arm, double-blind, phase III RCT. The study will recruit 460 patients (230 patients in each of the two arms) recommended for antireflux surgery from at least 16 centres in the UK and 7 other European high-volume upper gastrointestinal surgical centres. Patients will be randomized 1 : 1 to undergo either a laparoscopic/robotic LINX procedure or fundoplication. See *Fig. 1* for the study summary flow chart, *Fig. 2* for the data collection flow chart, and *Fig. 3* for the post-study care and follow-up flow chart.

**Fig. 1 znaf141-F1:**
[figure not shown]
Study summary flow chart GORD, gastro-oesophageal reflux disease; HRQoL, health-related quality of life.

**Fig. 2 znaf141-F2:**
[figure not shown]
Data collection flow chart GI, gastrointestinal; GORD, gastro-oesophageal reflux disease; HRQoL, health-related quality of life.

**Fig. 3 znaf141-F3:**
[figure not shown]
Post-study care and follow-up flow chart

### Population

The GOLF trial will recruit adults aged ≥18 years being considered for antireflux surgery for GORD insufficiently controlled by or intolerant to medical therapy. The inclusion and exclusion criteria are presented in *Table 1*.

**Table 1 znaf141-T1:** Inclusion and exclusion criteria for the GOLF trial

Inclusion criteria	Exclusion criteria
Age ≥18 years Willing and able to give informed consent GORD insufficiently controlled by medical therapy or intolerance to medical therapy and being considered for antireflux surgery Symptomatic and objectively defined GORD; endoscopy with appearances or biopsies consistent with reflux oesophagitis, or 24-h pH study or BRAVO test of the oesophagus consistent with GORD No hiatal hernia or hiatal hernia <5 cm in length Adequate lower oesophageal motility as defined by preoperative oesophageal manometry studies showing a mean contractile amplitude of >30 mmHg or distal contractile integral (DCI) of >450 mmHg per s per cm in 70% of swallows	Unsuitable for surgical intervention due to medical conditions precluding general anaesthesia Suspected or known allergies to titanium, stainless steel, nickel, or ferrous materials Previous antireflux or gastric surgery Previous or planned neurosurgery Oesophageal manometry showing complete absence of lower oesophageal contractility

GORD, gastro-oesophageal reflux disease.

#### Screening and recruitment

Participants will be recruited from hospitals in the UK and other European countries that regularly perform antireflux surgery. Potential participants will be identified during routine clinic visits and informed about the study through posters and Participant Information Sheets (PISs). If their usual care clinician is not part of the study team, patients will be asked for permission to share their contact details with the study team for follow-up.

#### QuinteT Recruitment Intervention (QRI)

The LINX procedure is not as well established as fundoplication. Recruitment is likely to be challenged by clinician and patient bias towards something new, potentially impacting eligibility decisions and how the treatments are presented. Furthermore, some centres may be less familiar explaining randomization to patients. A QRI has been included to understand and address recruitment challenges in real time^17–19^. The aim of the QRI is to assess the recruitment process at each recruiting site, to identify specific recruitment difficulties and tailor suggestions to change aspects of the design, conduct, or training that could lead to improvements in recruitment and informed consent.

A multifaceted, flexible approach will be used to investigate site-specific or wider recruitment obstacles, consisting of: mapping of eligibility and recruitment pathways to collate basic data about the levels of eligibility and recruitment, and to identify bottlenecks in recruitment pathways; in-depth semi-structured interviews with study and centre staff (and eligible patients if needed) to explore perceptions of the study and equipoise, how recruitment is organized in individual centres, and local or national challenges anticipated or encountered; audio-recording study recruitment discussions with potential study participants to offer direct insights into how the study is presented and ways in which recruiters manage patients’ expectations and preferences; and attendance at study meetings to gain an overview of trial conduct and overarching challenges.

The QRI team, with the Chief Investigator and Trial Management Group, will formulate action plans based on the findings to improve recruitment and information provision, with the format dependent on the nature of the recruitment barriers identified. Supportive and responsive group or individual feedback and training is likely to be a core component of the plan of action, including written recruitment ‘tips’ documents and suggested modifications to study pathways and patient-facing study material. The QRI work will be undertaken in an iterative and cyclical manner, continuing throughout the recruitment interval with close monitoring of changes in screening log data and recruiter practice to optimize recruitment and informed consent, all in close collaboration with the Chief Investigator and wider study team.

#### Laparoscopic or robotic LINX procedure (intervention)

The laparoscopic insertion of a magnetic ring, such as the LINX device, has been part of the NICE guidelines for treating GORD and therefore standard of care in the National Health Service (NHS) since 2017. Participants randomized to laparoscopic or robotic magnetic sphincter augmentation (LINX procedure) will undergo surgical treatment under general anaesthesia, with placement of the LINX device around the distal oesophagus. The LINX device consists of titanium beads with magnets in the centre.

#### Laparoscopic or robotic fundoplication (comparator)

Participants randomized to laparoscopic or robotic fundoplication will undergo surgical treatment for managing GORD, including a total or partial fundic wrap behind or in front of the distal oesophagus and gastro-oesophageal junction. According to several international guidelines, there is no convincing evidence at present to suggest a total or partial wrap to be superior to the other. As this is a pragmatic trial, all types of fundoplication will be recorded and form part of the subgroup analysis^8,20,21^.

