#### Translational ‘SQA’ substudy

SQA is an important component of this trial because LINX is a newer surgical procedure and because there is (inter)national variation in fundoplication techniques. This is the first trial of its kind to embed an SQA programme based on video analysis. The SQA will help to ensure the procedures are also completed to a good surgical standard, to maximize internal and external validity and facilitate accurate interpretation of trial results and replication of the successful intervention across wider clinical practice. Every operation performed within the trial will be video recorded and reviewed as part of the SQA programme.

The SQA programme will consist of five phases:

Surgeon training: Surgeons who have not previously undertaken the LINX procedure will attend a hands-on training day with Johnson and Johnson, followed by two proctored cases. A ‘gold standard’ demonstrative video will be circulated to all participating surgeons along with the competency assessment tools for the LINX procedure and fundoplication to ensure consistency.Credentialling of centres and surgeons: All surgeons who have performed <20 LINX procedures will be required to submit two videos each of them performing the LINX procedure and fundoplication, which will be assessed using a competency assessment tool (described below in phase 3).Standardization of surgical techniques: A competency assessment tool for the LINX procedure will be developed after a virtual Delphi consensus process and robust testing for inter- and intra-assessor reliability for video assessment. The Society of American Gastrointestinal and Endoscopic Surgeons (SAGES) has developed and validated a competency assessment tool for fundoplication, which will be used in the GOLF trial^22^.Mechanistic work: Video assessment will be undertaken for all operations performed within the trial to monitor learning curves and maintain surgical quality.Ongoing monitoring of adherence to the intervention protocols: This will be associated with correlating surgical quality with clinical and patient-reported outcomes.

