#### Non-inferiority outcome

A non-inferiority margin was set at two scores in difference on GORD-HRQoL based on a previous systematic review by the authors^13^, co-investigator consensus, and patient workshops. For a one-sided α level of 0.025 and expecting 10% loss to follow-up, 230 patients per group will be necessary to show non-inferiority with 90% power.

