### Randomization

Randomization will be performed using a minimization algorithm to ensure balance between the two treatment groups using stratification factors:

Age (<40, 40–60, and >60 years).Sex at birth (female and male).Co-morbidity at baseline according to the well-validated Charlson Co-morbidity Index (<2 and ≥2).BMI (<30 and ≥30 kg/m^2^).Preoperative DeMeester score (a composite score system of acid exposure during ambulatory pH monitoring used to objectively define GORD) (<14.7 and ≥14.7).Country of treatment (UK and non-UK).24 months after the surgery, patients will be unblinded (that is informed via letter or e-mail about which operation they underwent) and then they will be followed up according to the standard of care in their treating hospital.

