### Statistical analysis

All analyses will be carried out on the intention-to-treat population (that is all patients will be analysed in the group that they were randomized to regardless of the actual treatment received). It is not anticipated that there will be any protocol deviations; however, in the event that any occur, the primary analysis will be repeated for the per-protocol population (patients excluded from the per-protocol population will be pre-specified in the Statistical Analysis Plan).

Standard descriptive statistics will be used to describe the demographics between the two follow-up regimens; reporting means and standard deviations or medians and interquartile ranges as appropriate for continuous variables and numbers and percentages for binary and categorical variables. All comparative outcomes will be presented as summary statistics and reported together with 95% confidence intervals. All tests will be carried out at a 5% significance level.

The analysis of GORD-HRQoL will be performed using a linear mixed model. This model will produce as output an adjusted GORD-HRQoL score based on the fixed and random effects. It will consider, as the fixed effects, the intervention group, as well as the age, sex, BMI, and preoperative DeMeester score. It will consider, as the random effects, a random intercept by centre. An interaction between the random intercept centre and the intervention will also be included in the model. The model will be run and the output adjusted GORD-HRQoL scores will be compared.

The effect of the LINX procedure on GORD-HRQoL will be tested and quantified through mean differences between groups, adjusted for the factors included in the model; the 97.5% unilateral confidence interval of the mean differences will be provided. A transformation of the primary criterion may be performed to fulfil the assumptions of the linear mixed model.

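### The subgroup variable, type of fundoplication, exists only in the comparator arm and is not randomized, so contrasts based on the recorded type are not protected by randomization

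*Protocol article*

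**What the plan says.** All statements are in the Protocol article, Methods.

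- *Laparoscopic or robotic fundoplication (comparator)*: the comparator operation is described as "including a total or partial fundic wrap behind or in front of the distal oesophagus and gastro-oesophageal junction", and "all types of fundoplication will be recorded and form part of the subgroup analysis". It is the only subgroup analysis that the article names.
- *Design*: "Patients will be randomized 1 : 1 to undergo either a laparoscopic/robotic LINX procedure or fundoplication". The allocation is to an operation, not to a wrap.
- *Randomization*: "Randomization will be performed using a minimization algorithm to ensure balance between the two treatment groups using stratification factors". The factors listed are age, sex, Charlson index, BMI, DeMeester score and UK versus non-UK. Wrap type, intended wrap, surgeon and centre are not among them.
- *Translational 'SQA' substudy*: one reason given for quality assurance is that "there is (inter)national variation in fundoplication techniques".
- *Statistical analysis*: the analysis is by intention to treat, so "all patients will be analysed in the group that they were randomized to regardless of the actual treatment received". For the primary model, "It will consider, as the fixed effects, the intervention group, as well as the age, sex, BMI, and preoperative DeMeester score". A random intercept by centre and a centre-by-intervention interaction are added. Wrap type does not enter.

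**The concern.** A randomized subgroup analysis needs a variable that is defined for every patient and fixed independently of allocation. It can then compare the arms within each level and test whether the difference varies between levels. Type of fundoplication, as introduced here, meets neither condition: it describes something that happens in one arm only.

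What is at stake is the reading of this one analysis. Because the trial admits all wrap types, readers will probably ask whether the comparison with LINX depends on the wrap, for reflux control and for gas bloating. If patients who receive different wraps also differ in prognosis, or are treated in centres with different results, a difference in case mix could pass for an effect of wrap type.

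**Working it through.** The plan gives no figure for this analysis, so there is none to reproduce. The check is a reading of the sections against each other, followed by algebra that shows how the bias behaves.

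**Step 1. Is the variable defined in both arms?** It appears only in the comparator section and describes the comparator operation. LINX patients have no value. A model with treatment, wrap type and their product cannot be fitted to it, because one arm has no levels.

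**Step 2. Is it protected by the allocation?** No. Randomization is between LINX and fundoplication, and the six minimization factors include neither actual nor intended wrap. Under *Blinding*, the operating surgeon is told the allocation after randomization. Unless the wrap is declared earlier, nothing stops it from being settled with the allocation known.

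**Step 3. Which contrasts does the recorded type allow?**

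| Contrast | Groups compared | Randomized? |
|---|---|---|
| LINX versus one wrap type | A whole arm against part of the other arm | No |
| Wrap types within the fundoplication arm | Two parts of one arm | No |

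**Step 4. Would the planned adjustment repair this?** Only in part. Centre terms could absorb some differences between centres, and the four covariates some differences between patients. They do not cover other selection within a centre. Eligibility (Table 1) admits patients without a hiatal hernia and with one under 5 cm, for example, and hernia size is not in the model. The documents do not say that hernia size governs the wrap; the example shows only that unadjusted routes exist.

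**Step 5. How would a bias behave?** Suppose that neither treatment nor wrap type has any effect, that a share q of fundoplication patients receives a partial wrap, and that these patients score D points worse on prognosis alone. Set the total-wrap mean to 0. The partial-wrap mean is then D, and the LINX mean, a randomized mix of both kinds of patient, is qD.

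- LINX minus partial = qD − D = −(1 − q)D
- LINX minus total = qD − 0 = +qD
- Gap between the two contrasts = qD + (1 − q)D = D

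Neither q nor D is in the documents, so the values below are assumptions.

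| D | q | LINX − partial | LINX − total |
|---|---|---|---|
| 1 | 0.3 to 0.7 | −0.7 to −0.3 | +0.3 to +0.7 |
| 2 | 0.3 to 0.7 | −1.4 to −0.6 | +0.6 to +1.4 |
| 3 | 0.3 to 0.7 | −2.1 to −0.9 | +0.9 to +2.1 |

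The gap always equals the D that was put in. The table shows the mechanism and the opposite signs; it does not estimate a bias in this trial.

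**The case against.** The strongest reply is that the article gives this analysis a single clause. It does not state the contrast, the model, the time of recording or who chooses the wrap, and a condensed article may leave such matters to the full protocol or the SAP. That stands, and it limits what can be said. A reader might infer that the wrap is recorded as performed, that surgeons pick it patient by patient, and that LINX will be set against each wrap type. These are natural readings in a pragmatic trial, but the text says none of them.

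A reader might also conclude that no interaction could be estimated at all. That goes too far. Each surgeon's or centre's usual wrap would classify both arms, and the article does not rule this out. If wrap type varies mainly by centre, LINX patients in the same centres are natural controls. The only variation that the article documents is in technique, between and within countries; selection of patients on prognosis is nowhere described.

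Finally, a reader might set a 2-point bias beside the margin ("A non-inferiority margin was set at two scores in difference on GORD-HRQoL") and say that it consumes the whole margin. The documents do not support this. The 2 points would be an assumed prognostic gap handed back as a result, and the article sets the margin for the primary outcome without applying it to subgroups.

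The reply does not remove the central point. The article names the subgroup variable, and that variable exists in one arm. Either contrast in Step 3 is non-randomized, so the silence about which is meant does not help. Nor can an SAP written later create a pre-randomization declaration for patients already enrolled; it can only fall back on usual practice.

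**Conclusion.** The point holds, limited to the subgroup analysis by type of fundoplication. As written, the variable is defined only in the comparator arm and is neither randomized nor balanced by minimization. The recorded type supports no ordinary treatment-by-subgroup interaction, and any contrast built on it may be confounded by patient, surgeon or centre.

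The size and direction of the confounding cannot be derived from the documents. The conclusion assumes that the full protocol does not already classify both arms by a wrap declared before randomization or by usual practice; if it does, only the article's wording needs correcting. The intention-to-treat comparison of GORD-HRQoL and the core secondary outcomes, gas bloating and inability to belch, do not depend on wrap type and are not in question.

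**What to change.** 1. Before randomization, record for every participant the wrap intended if the allocation is fundoplication.
2. For patients already randomized, use the surgeon's usual wrap, or the centre's, established without reference to trial outcomes.
3. Base the subgroup analysis on a treatment-by-intended-wrap interaction across both arms, with each patient kept in the allocated arm and the intended-wrap stratum.
4. Present results by wrap actually performed separately, labelled non-randomized and descriptive.

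The cost is one field on the randomization form and a few lines in the SAP. The declaration need not bind the surgeon, so the choice of wrap is unchanged, as are the primary and core secondary analyses.

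The interaction will be imprecise. With equal arms, a common SD and a share q intending one type, ignoring covariates and centre effects, its standard error is 1/√(q(1 − q)) times that of the overall difference: 1/√0.25 = 2.0 at q = 0.5 and 1/√0.21 ≈ 2.2 at q = 0.3 or 0.7. It should be reported as an estimate with its confidence interval, and a non-significant test should not be read as showing that wrap type is irrelevant.
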